### Recruitment of Patients

Patients are consecutively being recruited from 3 hospitals, located in northern and central of Sweden. Inclusion criteria are breast, colorectal, or bladder cancer, age ≥ 18 years, scheduled for adjuvant or neo-adjuvant intravenous chemotherapy of moderate or high emetogenicity^
17
^ (Table 1), and physical, mental and linguistic capacity to give informed consent and participate in the study procedure, that is, understand information in the language of the study, that is, Swedish. Exclusion criteria include the presence of persistent nausea or ongoing antiemetic treatment before the very first chemotherapy session—specifically, if symptoms persist into the day before initiating chemotherapy—as well as a diagnosis of hemophilia. Additionally, any prior participation in the study (such as during a recurrence or following relocation from another city) will exclude patients from enrollment.

**Table 1. table1-15347354251361464:** The Chemotherapy Agents.

Chemotherapy agents	Highly emetogenic chemotherapy agent, HEC	Moderately emetogenic chemotherapy agent, MEC	Low emetogenic chemotherapy agent, MEC
Cisplatin	X		
Carboplatin		X	
Irinotecan		X	
Cyclophosphamide <1500 mg/m^2^		X	
Doxorubicin		X	
Epirubicin		X	
Oxaliplatin		X	
Mitomycin			X
Paclitaxel			X
Docetaxel^ a ^		X	
5-Fluorouracil			X
Gemcitabine			X

Some patients receive LEC combined with MEC or another LEC. When 2 or more agents are combined the emetogenic potential essentially becomes 1 grade higher than that of the most emetogenic agent in the combination. Those patients thus receive highly or moderately emetogenic chemotherapy and are eligible for this study.

a Considered as moderately emetogenic according to the local guideline implemented at the studied clinics like in previous versions of international guidelines, applied when starting the data collection. The recently updated guideline^
17
^ considers Docetaxel to be of low emetogenicity.

Oncology nurses at the oncology departments are consecutively identifying patients scheduled for chemotherapy, asking if the patients are interested in receiving information about the study, and if they are, the nurses send study information by post. Next, the study coordinator of each department contacts the patients, providing the study information verbally and giving opportunities to ask questions. The written and verbal information states that patients will be randomized to receive antiemetics according to standard care routines or standard care combined with 1 of 2 types of acupuncture needling procedures: one that penetrates the skin and one where the needles are placed against the skin. Neither of the acupuncture needling procedures is described as a sham treatment. Further, the information states that the treatment types will be given using 2 types of “treatment procedures” performed by the intervention therapist, without any further specification, the goal being to prevent patients from knowing too much about the exact contents of the communication styles. Patients who agree to participate in the trial give their written informed consent.

Participants are scheduled to complete the study procedure during the chemotherapy session immediately following inclusion. However, certain exceptions to this plan may occur. The combination of chemotherapy agents varies according to each patient’s individual cancer treatment plan. If the next scheduled session involves only low-emetogenic agents (ie, no moderate-to-high emetogenicity), the study procedure will instead take place during the subsequent session. Practical considerations—such as treatment being administered at a different hospital or the intervention therapist being unavailable—may also necessitate postponing the study procedure to a later session. In these cases, participants will be involved in the study procedure during the next appropriate chemotherapy session. We will document the total number of chemotherapy sessions administered prior to the study session and record the emetogenicity levels of the agents used (see chapter Data collection, on medical record clinical data).

### Randomization and Blinding

Using a computerized randomization table, a statistician randomizes the patients, stratified for hospital, to 1 of the 2 communication styles (1 or 2) conducted during 3 treatment types (Type A, B, or C; Figure 1) without applying any block randomization. After the intervention therapist initially conducts the physiological measures described below, he/she receives the randomization result from the randomization table and begins the study procedure in line with the randomization result (Figure 2), according to a standardized treatment protocol. The patients and all medical and healthcare personnel, other than the intervention therapist delivering the standardized treatment protocol procedures, are blinded to the acupuncture and communication allocation (see description of treatment types below). The evaluator is blinded to allocation until after analysis of the primary outcome. This is possible because all patients and allocation groups are coded; the evaluator does not know which code means which allocation group until thereafter.

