**Methods::**

This is a trial protocol for a randomized, sham-controlled, patient- and evaluator-blinded clinical trial. Patients (n = 198 patients according to a sample size calculation) with breast, colorectal, or bladder cancer undergoing neo-/adjuvant moderately to highly emetogenic chemotherapy are being randomized in 2 × 3 factorial design to the following conditions: 1. neutral or 2. positive communication style regarding expected treatment effects, during the antiemetic treatment types: A) standard care only (including antiemetics, no acupuncture), or, in addition to standard care, B) sham acupuncture with telescopic non-penetrating needles, or C) verum, penetrating acupuncture. The 2 communication styles 1 and 2 are carried out during the antiemetic treatments given by an intervention therapist immediately pre and post (20 minutes × 2) an intravenous chemotherapy session. Data are being collected at baseline on the day before the chemotherapy session, daily for 10 days, at a 10-day follow-up, and at a follow-up after completing the entire chemotherapy period, lasting about 6 months. Primary outcome is mean score Visual Analog Scale nausea grading for the first 5 days of the chemotherapy session period. Secondary outcomes are for example, vomiting, treatment expectations, QoL, daily and physical activity, and physiological measures. Treatment effect modifiers will be analyzed, for example, blinding success, treatment expectations, and previous nausea experiences.

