The main study hypothesis is that positive communication plus acupuncture (penetrating verum or non-penetrating sham acupuncture) is more effective than neutral communication plus standard care for nausea, calculated as the mean score for the first 5 days of the studied chemotherapy session period. We hypothesize that treatment expectation is a mediator of the effects.

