### Data Analysis Plan

The intention-to-treat principle will be applied when analyzing the study data, that is, all patients will be analyzed as randomized, regardless of whether they complete the study procedure as planned. The primary parameters of interests are the 2 factorial effects (2 main effect, ie, 1. communication style, and 2. treatment type, and one interaction, ie, treatment expectations) during the first 5 days of the studied chemotherapy session period. The evaluator will use a generalized linear mixed effects model (GLMM) to determine if the independent variables communication style and treatment type affect the dependent variable nausea. We take the stratified randomization into account (adjusting for random effects of department on the outcomes) and include baseline characteristics in the analysis model to increase the precision of the estimates.^
77
^ In secondary GLMMs, we will study the effects of the variety of independent variables on vomiting, QoL, and daily and physical activity. Patients who cease to participate (dropouts) and missing data will be handled according to routines as follows. In the main analysis, missing data will be handled using multiple imputations by chained equation.^
78
^ We will specify the multiple imputation model (the choice of auxiliary variables) after comparing patient characteristics between those with complete and those with incomplete data. Under the assumption that data are missing at random, an analysis based on multiple imputation conforms with the intention to treat. We will then also estimate the factorial effects using complete data only. We will conduct a sensitivity analysis by comparing estimates regarding the 2 main effects described above with estimates based on complete data only, in other words, a pattern-mixture model and tipping point analyses. Statistical significance will be defined as a 2-tailed *P* < .05, and the analyses will be performed in IBM SPSS statistics (IBM Corp, Armonk NY, USA).

In line with previous recommendations regarding cost-effectiveness analysis alongside clinical trials, we will specify the methods for cost effectiveness analysis after evaluating these outcomes. If the present evaluation shows significant health benefits on the primary outcome measure, or in at least on 1 secondary outcome, a cost-effectiveness analysis of our intervention will be conducted using a model-based approach.^
79
^

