^ the next natural step will be to present the current large-scale, well-designed study, addressing what constitutes optimal communication for obtaining effects on nausea and vomiting and for improving QoL and capacity in daily and physical activities among patients undergoing chemotherapy. The patients participate in the study during one chemotherapy session, and thus the primary outcome is based on data collected within that session. To intervene with the patients and thus collect data during the entire chemotherapy period for about 6 months was valued to be unethical. We want to minimize the burden of the study on this rather frail patient group until we become aware of the efficacy of the treatment types and the communication styles. If positive communication added to antiemetic treatment is effective, this integrative cancer therapy intervention may be implemented during the entire chemotherapy period. The underlying mechanisms of nausea and vomiting are complex and involve a wide range of biopsychosocial mechanisms.^
35
^ To identify potential *psychological* mechanisms mediating beneficial effects of antiemetic acupuncture, treatment expectations will be analyzed. To identify potential *biological* mechanisms underlying beneficial effects of antiemetic acupuncture, the stress indicators blood pressure, heart rate and cortisol concentration in saliva will be analyzed. The data collection procedures thoroughly collect data on previous nausea experiences, since exposure to emetogenic situations and to previous nausea increases the risk for developing nausea.^2,4,36^

The research team involving and surrounding the authors includes experts in integrative medicine, nursing, physiotherapy, psychology and behavioral medicine, oncology, cell biology, and health economy, thus enabling a broad-based approach to gain new knowledge. The study will contribute knowledge that can be used when treating patients in clinical practice by evaluating the role of healthcare personnel’s communication and patients’ treatment expectations, as well as the use of different antiemetic strategies, that is, using antiemetics alone or antiemetics plus acupuncture. Evaluating the effects of communication and antiemetic therapy as well as identifying moderating and mediating variables on our outcome—nausea—may be expected to be beneficial on at least 3 levels. Individual gains of reduced nausea may include improved self-perceived QoL,^6

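### The evaluator's blind is promised only up to the primary analysis; extending it to the sensitivity and secondary outcome models would be a cheap, low-priority improvement

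*Protocol article*

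**What the plan says.** The protocol article, under Randomization and Blinding, sets the limit of the evaluator's blind: "The evaluator is blinded to allocation until after analysis of the primary outcome". It explains that patients and groups are coded and that "the evaluator does not know which code means which allocation group until thereafter". No later section extends the promise.

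The Abstract (Methods) and the end of the Introduction both call the trial evaluator-blinded, with no restriction to one outcome.

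The Data Analysis Plan assigns the primary model, for nausea, to the evaluator: "The evaluator will use a generalized linear mixed effects model (GLMM) to determine if the independent variables communication style and treatment type affect the dependent" (quote cut short here). It then describes complete-data, pattern-mixture and tipping-point checks. On the other outcomes it says: "In secondary GLMMs, we will study the effects of the variety of independent variables on vomiting, QoL, and daily and physical activity". Further analyses are announced in other places:

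- **Modifiers** (Abstract): "Treatment effect modifiers will be analyzed, for example, blinding success, treatment expectations, and previous nausea experiences".
- **Mediation** (Introduction): "We hypothesize that treatment expectation is a mediator of the effects".
- **Physiology** (Discussion): "the stress indicators blood pressure, heart rate and cortisol concentration in saliva will be analyzed".
- **Health economics** (Data Analysis Plan): "we will specify the methods for cost effectiveness analysis after evaluating these outcomes". This analysis goes ahead if the primary outcome or at least one secondary outcome shows a significant benefit.

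**The concern.** Evaluator blinding in this trial protects analytic judgement, not measurement, since the evaluator rates nothing. Its value is that choices about covariates, outcome handling and missing data are made without knowing which choice favours positive communication or acupuncture. Under the stated rule that protection may end after a single outcome.

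Much of the trial's purpose lies beyond that outcome. The objectives in the Introduction name vomiting, quality of life, and daily and physical activity beside nausea, and expectation is the hypothesised mechanism. One significant secondary result is enough to launch the economic evaluation. If the key is released early, these results could come from an analyst who knows the arms and the direction of the primary result, while a reader of the label evaluator-blinded would assume otherwise.

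**Working it through.** No arithmetic applies: the plan gives no figure on this point. The check sets the passages side by side.

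**1. Which analyses does the stated blind cover?**

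| Analysis | Where announced | Covered by the rule? |
|---|---|---|
| Primary model, 5-day mean nausea | Data Analysis Plan | Yes |
| Complete-data, pattern-mixture and tipping-point checks | Data Analysis Plan | Unclear: the rule does not say whether they belong to the primary analysis |
| Vomiting, quality of life, activity models | Data Analysis Plan | No |
| Expectation as mediator | Introduction, Discussion | No |
| Blood pressure, heart rate, cortisol | Discussion | No |
| Effect modifiers | Abstract | No |
| Cost-effectiveness | Data Analysis Plan | No; methods expressly left until outcomes are evaluated |

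**2. When could the code be released, compared with when the data are complete?** The primary outcome uses the chemotherapy day and the four days after it (Sample Size). Data Collection continues with the diary to day 10, then a questionnaire 10 days after the whole regimen, which typically lasts about 6 months. Nothing ties release of the code to the last follow-up or to a data lock. Data Collection also says that responses are handled only by the independent evaluator. The rule therefore permits, without requiring, late secondary data to be handled by someone who already holds the key.

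**3. Can the uncovered analyses be run on coded groups?**

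- *Sensitivity, secondary outcome and mediation models:* yes. They use the same two coded factors as the primary model, with a different outcome, different handling of missing data, or the expectation rating added.
- *Blinding success:* no. Deciding whether a patient guessed the needle type correctly requires the true allocation.
- *Other items that give the arm away:* standard-care patients tick a not-applicable option on the needle question, only the two acupuncture types grade needle pain, and therapists log points treated, stimulations and phrases delivered. Opening these variables decodes the groups.

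The coding therefore already serves most of the uncovered work, and a small, identifiable set of analyses has to wait for the key.

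**The case against.** The strongest reply is that nothing here is wrong. The protocol states openly where the blind ends, and that qualifies the general label. The primary analysis is covered. Nausea, vomiting, quality of life, activity and expectation are self-reported, so a later unblinding of the analyst cannot change the recorded values. All of this stands, and it is why the point is an improvement and not an error.

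Several stronger readings are tempting but are not supported:

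- *The code is broken as soon as the primary analysis is done.* The wording sets an earliest point. It gives neither an immediate release nor an order for the later analyses.
- *All secondary, modifier and mechanism models are chosen afterwards.* The secondary model class and outcome domains, three example modifiers, the mediator and the physiological variables are named in advance. A statistical analysis plan that is not shown may fix the predictors, so open lists in an article are no finding. Only the cost-effectiveness methods are expressly deferred.
- *The same evaluator certainly fits the secondary models.* The plan names the evaluator for the nausea model but writes in the first person plural for the others.
- *The shortened blind inflates the false-positive rate by a calculable amount.* Picking the smallest two-sided P value over several models gives the same result with coded arms as with named ones. A simulation of that kind measures lack of pre-specification, not unblinding. Knowing the codes adds the ability to favour a particular direction, and the documents give no basis for sizing that.
- *Every analysis could be run blind.* Blinding success and the arm-revealing items cannot.

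What survives is that an analysis plan with fixed models would reduce the discretion but would not by itself alter the stated rule on when the code may be released.

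**Conclusion.** The concern holds in a limited form. The promise of evaluator blinding stops at the primary outcome. The sensitivity analyses are left ambiguous, the secondary outcome and mediation models have no stated protection, and code release is not linked to the end of follow-up. The primary result and the measurement of outcomes are unaffected.

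No numerical size can be given. In practice the exposure depends on three things the document leaves open: when the key is actually released, who fits the later models, and how much an analysis plan fixes beforehand. If the models are locked before release, little remains. Low priority, but worth doing, because the coding already in place serves the secondary outcome models as well.

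**What to change.** Amend the sentence in Randomization and Blinding to say, in substance:

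- The evaluator remains blinded until follow-up data are locked and the primary, sensitivity, secondary outcome and expectation-mediation models have been run on coded groups.
- The key is kept by a person outside the analysis.
- Analyses that need or reveal true allocation (blinding success, needle pain, therapist adherence items) have their scripts fixed before the code is released and are run last, or are labelled exploratory.

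Variables that reveal the arm should be held back from the coded analysis file until that last step.

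Cost: the key is held longer, possibly until the last patient's end-of-regimen questionnaire, and some scripts must be written earlier. Data collection is described as ongoing, so the change may still be possible. If the key has already been released, report when this happened and which analyses came after it.

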**Figure 3. fig3-15347354251361464:**
[figure not shown]
Schedule of enrollment, intervention and assessment (SPIRIT). ^
1
^Measured immediately post intervention. ^
2
^Therapist data were only collected once, preceding study involvement. FACT-G: Functional Assessment of Cancer Therapy-General; QoL: quality of life; EQ-5D-3L: Euroqol 5 dimensions, 3 levels; EQ-VAS: Euroqol Visual Analog Scale; NBHW-PAI: National Board of Health and Welfare’s Physical Activity Indicator Questions.

Independent of patients’ cancer care, the study coordinator at each department sends the baseline questionnaire and the daily nausea and vomiting measure to patients by post or e-mail, according to the preferences patients expressed during the telephone call when study information was provided. The intervention therapists give patients the 10-day follow-up questionnaire and the completion questionnaire directly after conclusion of the study intervention, clearly stating that “these questionnaires come from the evaluator, and I will not be aware of your answers.” Patients may answer the different questionnaires using either “pen and paper” or the study’s digital web questionnaires, according to their own preferences. The study information ensures patients that their responses (marked by an identification code instead of any personal information) will not be managed by the cancer care personnel, only by the independent study evaluator.

About 1 to 2 weeks after an expected response, the study coordinator sends a gentle reminder through the post to those who have not yet responded, and after responding to the completion questionnaire, patients receive a letter, sent via post, expressing our gratitude for their participation. Figure 3 presents the measurements described below.

Medical record clinical data: Research nurses of the oncology departments collect data from patients’ medical records regarding cancer diagnosis, disease-specific variables, types, doses and frequency of chemotherapy, and if the patient was chemotherapy-naïve or not when participating in the study. Data on the types and doses of prophylactic antiemetics given to the patients are also collected, for the entire chemotherapy period.

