The analyzer at the laboratory of each hospital at the study sites analyzes the samples using an enzyme immunoassay kit (Salimetrics LLC, USA). Regarding the precision of the measurements, the total coefficient of variation is 13.3% at 3.4 nmol/L and 6.3% at 29.4 nmol/L. The detection limit is 0.3 nmol/L. If the analyses cannot be done consecutively, the laboratory may store the samples at −20°C for up to 9 months.^
71
^ In the event of storage, the samples will be thawed at room temperature and centrifuged at 1500*g* before assay.

Treatment adherence, complications, and blinding data: At every treatment session, the intervention therapists register their adherence to the study protocol (eg, treated acupuncture points, number of needle stimulations, delivered verbal phrases). The intervention therapists register potential negative side-effects or complications occurring during the treatment sessions.

At the 10-day follow-up measure, patients respond in a binary fashion to a blinding measure^
59
^: “Do you think you have been treated with needles that have penetrated your skin, or do you think the needles have only been placed against the surface of your skin?” They also grade how certain they feel on the accuracy of their response: “Not sure at all, just guessed,” “fairly sure,” “entirely sure.” If patients have received standard care only, they choose the additional alternative “Not applicable, I did not receive any acupuncture treatment.” They respond to the question^
51
^: “During your chemotherapy session, you met an intervention therapist. Do you think you have received treatment from a therapist who emphasized the expected positive effects or one who did not?” This is measured using a 100 mm VAS anchored with 0, “Communicated very negative” and 100, “Communicated completely positive.” Patients in treatment type B-C grade their self-perceived needle-induced pain (“No/little/moderate/very painful”) and register potential side-effects of the acupuncture treatment.

Co-occurring symptoms, consumption of co-interventions: Patients repeatedly grade experience of co-occurring symptoms/problems, fatigue,^
72
^ sleeping quality,^
73
^ anxious and depressed mood,^
74
^ relaxation,^
51
^ pain and unpleasant symptoms (ie, neuropathy symptoms),^
75
^ wellbeing,^
37
^ eating capacity,^
76
^ and stool frequency.^
57

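### Group coding cannot keep the evaluator blind to standard care versus acupuncture, because the day-10 answers the evaluator manages identify the standard-care patients

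*Protocol article*

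**What the plan says.** The Abstract and the Introduction of the protocol article describe the trial as patient- and evaluator-blinded. Randomization and Blinding makes this specific: "The evaluator is blinded to allocation until after analysis of the primary outcome". The only mechanism given is coding of patients and groups, so that "the evaluator does not know which code means which allocation group until thereafter".

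Three other places bear on this.

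- **Who holds the answers.** Under Data Collection, patients are told that their coded responses "will not be managed by the cancer care personnel, only by the independent study evaluator".
- **Who runs the primary analysis.** The Data Analysis Plan assigns the mixed model for nausea to the evaluator. It also says the auxiliary variables for the imputation model will be specified after patients with complete data have been compared with those with incomplete data.
- **What the day-10 form contains.** In the paragraph on treatment adherence, complications and blinding data, patients who had standard care only are given the response "Not applicable, I did not receive any acupuncture treatment". By contrast, "Patients in treatment type B-C grade their self-perceived needle-induced pain", and the same patients report side-effects of the acupuncture. All patients rate on a VAS how positively the therapist communicated.

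**The concern.** A code hides allocation only if nothing attached to it shows what it stands for. Here the person who is meant to be blind manages a questionnaire in which one response means that the patient had no needles, while other items apply only to patients who had them. Coding, the one safeguard stated, does not protect that distinction.

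The distinction is not peripheral. The main hypothesis (end of the Introduction) sets positive communication plus verum or sham acupuncture against neutral communication plus standard care, and treatment type is one of the two main effects in the Data Analysis Plan. An evaluator who can tell A from B and C can see one of the two dimensions of that contrast while the imputation model for the primary outcome is still open.

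**Working it through.** The article gives no figure for this point, so the check is a trace of who sees what, followed by a count of how far the codes can be read.

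**Step 1: data flow.** The claim is that the evaluator is blind until after the primary analysis, by coding. The evaluator manages the responses and fits the model. The primary outcome covers the first 5 days, and the revealing items arrive with the 10-day follow-up. The article describes no separation of these items from the primary analysis. It does not say when the evaluator opens them or when group codes are joined to them.

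**Step 2: which contrasts have exclusive answers.**

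| Contrast | Answer exclusive to one side? |
|---|---|
| A versus B/C | Yes: the not-applicable response (A); needle pain and acupuncture side-effects (B/C) |
| Sham versus verum | No: both needle groups answer the penetration question, and the sham device is described as credible |
| Neutral versus positive | No: every patient answers the same VAS |

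**Step 3: labelings left open.** The article does not say how the groups are coded.

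- Six cell codes: 6! = 720 possible labelings. With the two A codes recognised, 2! × 4! = 48 remain.
- Codes kept per factor (2 styles, 3 types): 2! × 3! = 12. With A recognised, 2! × 2! = 4 remain.

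The exclusive answers settle A and nothing else.

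**Step 4: how certain A is.** Assume equal cells, 198/6 = 33, hence 2 × 33 = 66 standard-care patients. Because randomization is unblocked, this is an expectation. Assume also that each responding standard-care patient picks the intended response. The chance that a given A cell shows it at least once is 1 − (1 − r)^33 for day-10 response rate r:

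- r = 0.10: 1 − 0.9^33 = 0.969; for both A cells, 0.969² = 0.939
- r = 0.50 or more: essentially 1

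If a single code covers all 66, r = 0.10 gives 1 − 0.9^66 = 0.999.

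**Step 5: communication style.** The article gives no SD and no expected difference for the communication VAS, so this is illustration only. Assume SD 25 mm. The SE of a difference between two means of n patients each is 25 × √(2/n): 6.2 mm for n = 33 and 3.6 mm for n = 99.

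| Assumed true difference | Two cells of 33 known to share a treatment type, ordered correctly | Four B/C cell codes, pairing unknown, split correctly (simulation) | Two style codes of 99, ordered correctly |
|---|---|---|---|
| 5 mm | Φ(0.81) = 0.79 | 0.51 | Φ(1.41) = 0.92 |
| 10 mm | Φ(1.62) = 0.95 | 0.84 | Φ(2.81) = 0.998 |
| 20 mm | Φ(3.25) > 0.99 | > 0.99 | > 0.99 |

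The answer runs from about even odds to near certainty, depending on an unknown difference and an unstated coding scheme. No size can be attached to this part.

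**The case against.** The strongest reply has four parts.

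*The sentence on who manages responses is a confidentiality assurance, not a data-flow specification.* This is fair. When codes are joined to the day-10 items is not stated, and the contents of the blinded analysis file may be set out in a full protocol or SAP that is not shown. But the point is not that detail is missing. The article positively says that coding makes the blind possible, and its own day-10 form shows that coding alone does not do so for A versus B/C.

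*Nausea is rated by the patient in a diary.* This stands. An unblinded evaluator cannot alter the ratings, so a reader should not infer biased outcome assessment. What remains exposed is the choice of analysis.

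*Little is left to choose.* This largely stands. The model type, the department adjustment, multiple imputation by chained equations, the complete-data analysis and the tipping-point analyses are all named. The text says baseline characteristics enter the model; it does not say they are picked after the data are seen. Only the imputation auxiliaries are explicitly deferred to the data, and the stated basis is complete versus incomplete patients rather than allocation.

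*The remaining codes are not shown to be readable.* This stands. A reader might infer that communication style, the contrast on which the sample size rests, is decoded as well, or sham versus verum. No answer is exclusive to either side of those contrasts, and any probability for style depends on assumed inputs. A reader might also infer that the therapists' adherence records disclose allocation to the evaluator. The article says only that therapists register those data, not that the evaluator receives them.

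**Conclusion.** The concern holds in a limited form. The stated reason for the evaluator's blind fails for standard care versus acupuncture: about 66 of 198 patients, identifiable with near certainty once codes and day-10 answers are linked. This assumes roughly equal cells, standard-care patients choosing the response provided for them, and linkage before the primary analysis, which is a reasonable inference but not a stated fact.

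Sham versus verum is not reliably decoded. The communication VAS may hint at style, to a degree that the documents do not let anyone derive. The consequence is limited to analysis decisions on the primary outcome, in practice the imputation auxiliaries. It is worth correcting because evaluator blinding is a headline design property, the affected distinction is part of the main-hypothesis contrast, and the repair is cheap.

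**What to change.** Amend Randomization and Blinding in two respects.

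1. The statistician who holds the randomization table releases group codes to the evaluator only after the covariates, the imputation model and the primary analysis code are fixed.
2. Until the primary analysis is locked, the primary analysis file with codes excludes the day-10 needle-guess, needle-pain, acupuncture side-effect and communication-VAS items, and the therapists' forms. The same items should stay out of the file on which the imputation choices are made, because a not-applicable answer marks an individual patient as standard care even without a group code.

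Delaying the codes is preferable to passing the day-10 answers to the departmental study coordinators, which would conflict with the assurance given to patients about who manages their responses.

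If this is not practicable, the alternative is to limit the claim so that evaluator blinding does not cover standard care versus acupuncture.

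The cost is a short text change, a restricted export and agreement on when codes are released. No patients, visits or procedures are added. Two drawbacks remain. The withheld items cannot serve as auxiliaries in the primary imputation. And because the evaluator still has custody of the forms, the restriction works only if the withheld day-10 items stay unopened, or at least unexported, until lock. Recruitment is already under way, so the current handling of returned forms should be checked first.
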